**Fig. 1 Fig1:**
[figure not shown]
Study flow chart

## Methods

### Trial setting

Denmark is a decentralized health system where the national government provides block grants from tax revenues to the five regions and 97 municipalities who deliver health care services. All residents are entitled to publicly financed health care. The five regions are responsible for hospital care, including emergency care, psychiatry, and for health care services provided by general practitioners (GPs) and medical specialists working in private practice. Danish GPs (*n* = 3,326) are self-employed, predominantly work in partnership practices, and work on contract for the public funder [30, 31]. Most patients with T2D are followed in general practice. Endocrinologists working in hospitals provide written support and phone counselling to GPs regarding treatment of patients with T2D.

### Trial participants

General practice: All general practices (including general practitioners and clinical staff) located in the Municipality of Aarhus are invited (*n* = 100). Participation is remunerated. Hospital: Endocrinologists from Steno Diabetes Center Aarhus, Aarhus University Hospital.

### Eligibility criteria

General practices are eligible for inclusion if licensed and located in the municipality of Aarhus. GPs must consent to participate in the intervention and collect the data needed to measure patient and general practice outcomes. A hospital secretary will collect the signed informed consent to participate in print before randomization. General practitioners must be willing to bring patient cases to the virtual conferences who are ≥ 18 years, diagnosed with T2D and who they would like to discuss with the endocrinologist.

The endocrinologists from Steno Diabetes Center Aarhus must be trained as endocrinologist with speciality in diabetes and provide written informed consent to participate in the intervention.

### Intervention

#### Method used for the intervention development

The intervention was developed using the Medical Research Framework for developing complex interventions [26, 27]. The intervention development process (Additional file 2) consisted of iterative cycles of adjusting the intervention, in which two approaches were combined to gain methodological strength: a partnership- and evidence-and-theory based approach [32]. The evidence-and-theory based approach consisted of using the behaviour change wheel method including a COM-B (capability, opportunity, motivation, behaviour) in addition to the MRC framework [33]. Throughout the process, a programme theory guided the intervention development.

Small-scale feasibility tests had been conducted in other municipalities from the Central Region Denmark, which the municipality of Aarhus also belongs to. Evaluations of the feasibility tests showed that the intervention was implementable in daily clinical practice and that general practitioners, practice staff, and endocrinologist were satisfied with the content and results of the intervention.

#### Intervention arm

Table 1 provides a detailed description of the intervention according to the *Template for Intervention Description and Replication checklist and guide* (TIDieR) [34]. The intervention consists of four virtual conferences (45 min) between endocrinologists and an individual general practice that take place over a period of 12 months (month 2, 5, 8, and 11). Before having the first virtual conference, an introductory webinar (90 min in month 1) is held to learn GPs about how to use the electronic “Diabetes Overview” to identify and manage patients with T2D.

**Table 1 Tab1:** Intervention according to TIDieR (Template for Intervention Description and Replication)

Brief name	Virtual specialist conferences between general practitioners and endocrinologists about type 2 diabetes
Why	To support general practitioners (GP) in managing their patients living with type 2 diabetes (T2D). To optimize pharmacological treatment of patients with T2D
What	Virtual conferences between GPs and endocrinologists lasting approx. 45 min. The four conferences are thematic: (1) T2D and cardiovascular disease and heart failure, (2) T2D and cholesterol and lipids, (3) T2D and kidney disease and blood pressure, and (4) T2D and a free topic. The GP is asked to bring to each conference 2–3 patient cases related to the theme and 1–2 patient cases of their own choice. Each conference follows the same format: (1) check in (5 min), (2) presentation by endocrinologist on the conference theme with a focus on medication and treatment guidelines (10 min), (3) presentation by GP and joint dialogue about 2–3 patients related to the theme (20 min), (4) presentation by GP and joint dialogue about 1–2 patients unrelated to the theme (optional; 5 min), and (5) wrapping up and summary of learning points (5 min) Before the first virtual conference, an introductory webinar (90 min) is held to learn GPs about how to use the electronic “Diabetes Overview” to identify and manage patients with T2D All conferences and webinars are carried out according to a manual
Who provided	Preparation and roles before and during virtual conferences: GP(s): - Chair of the meeting - Finds patient cases via “Diabetes Overview” - Presents patient cases General practice staff: - Participates in the dialogue Endocrinologists from Steno Diabetes Center Aarhus. Each general practice meets the same endocrinologist in all the conferences: - Presentation on the conference theme - Dialogue about and advises on patient cases
How	Virtual conferences between one endocrinologist and at least one GP from each general practice. MDs in training and practice staff from the general practice is encouraged to participate The virtual conference is integrated into the working plan of the endocrinologists GPs are responsible for planning their own clinical programme
Where	Virtual meeting platform. The endocrinologists will be sitting at Aarhus University hospital. The GPs will be sitting in their practice or at home
When and how much?	Each general practice will receive four conferences in 1 year each lasting approx. 45 min and one introductory webinar (90 min)
Tailoring	GPs decide themselves on which patient cases they want to bring to the conferences: 2–3 related to the theme and 1–2 patient cases of their own choice
Modifications	Modifications due to changing circumstances or on behalf of the participants will be noted throughout
How well	Adherence and fidelity in the outcome study is analysed, and the trial will study process outcomes

Each general practice is assigned to an endocrinologist who they meet at all four conferences. The four virtual conferences are thematic: [1] T2D and cardiovascular disease and heart failure, [2] T2D and lipids, [3] T2D and kidney disease and blood pressure, and [4] T2D and a free topic selected by the GP. The GP is asked to bring two–three patient cases to each conference who are related to the theme and one-two patient cases of their own choice. The GP chairs the meeting. Each virtual conference follows the same format: [1] check in (5 min); [2] short presentation by the endocrinologist on the conference theme with a focus on medication and treatment guidelines (10 min); (3) presentation by GP and joint dialogue about 2–3 patients related to the theme (20 min); (4) presentation by GP and joint dialogue about 1–2 patients unrelated to the theme (optional; 5 min); and (5) wrapping up and summary of learning points (5 min).

Conferences and webinars are carried out according to a manual. The intervention will not be modified during the study period. The general practices in the intervention group will transition to a maintenance phase (month 12 to 24) where they get a maximum of two virtual specialist conferences.

#### Comparison arm

General practices allocated to the control group will continue to get access to the usual written or telephone support by an endocrinologist in hospitals. This requirement to provide diabetes support to GPs is part of a collective agreement between the Danish Regions and the Association of General Practitioners [35]. The control group will get the intervention after the primary intervention ends, that is, after month 12.

#### Concomitant hospital support

In both arms, general practices can contact the hospital and the Steno Diabetes Center Aarhus as they please. The frequency of other contacts will be measured in the survey to GPs.

### Assignment of interventions

Block randomization is performed at the general practice level. General practices will be randomized in a 1:1 ratio to either the intervention or the control group by a statistician, according to a computer-generated list, independent of the measurement team. Randomization included stratification by number of full-time GPs and geographic location. The latter because general practices located in the centre and periphery of the municipality of Aarhus differ in patient demographics. A hospital secretary will be in charge of enrolment of participants.

### Outcomes

#### Clinical outcomes

Table 2 shows the primary and secondary patient outcome measures. The primary patient outcomes are the percentage of patients with T2D and three types of co-morbidities on appropriate diabetes-related medication: ischemic heart disease and/or stroke; micro- or macro-albuminuria; and LDL > 2.5 mmol/L. To account for multiplicity, we use the Bonferroni correction method to adjust the *p*-values of the three primary clinical outcomes. The Bonferroni correction sets the significance cut-off at α/n [36], which means we only reject the null hypothesis of a primary clinical outcome if the *p*-value is less than 0.0167 (i.e., 0.05/3).

**Table 2 Tab2:** Overview of primary and secondary outcomes measures

Aspect	Outcome measure
Primary clinical outcome measures	Percentage of patients with T2D and ischemic heart disease and/or stroke being treated with glucagon-like peptide 1 receptor agonists (GLP1-RA) and sodium glucose cotransporter 2 (SGLT2) inhibitor
	Percentage of patients with T2D and micro/macro-albuminuria being treated with angiotensin-converting-enzyme-inhibitor (ACE) or angiotensin-2-receptorantagonist (AT2)
	Percentage of patients with T2D and LDL > 2.5 mmol/L being treated with statins
Secondary clinical outcome measures	Percentage of patients with T2D and HbA1c < 58 mmol/L
	Percentage of patients with T2D and HbA1c < 53 mmol/L
	Percentage of patients with T2D and blood pressure < 140 mmHg
	Percentage of patients with T2D and blood pressure < 130 mmHg
	Percentage of patients with T2D and low-density lipoprotein > 2.5 mmol/L
	Percentage of patients with T2D and microalbuminuria and LDL > 1.8 mmol/L
Primary competence and organization outcome measures	The extent to which the GP is confident managing T2D in general
	The extent to which the GP is skilled in making decisions on T2D in general
	The extent to which the GP is confident managing T2D and ischemic heart disease, stroke, peripheral artery disease, and heart failure
	The extent to which the GP is confident managing T2D and blood pressure
	The extent to which the GP is confident managing T2D and kidney disease
	The extent to which the GP is confident managing T2D and cholesterol
Secondary competence and organization outcome measures	GPs rating of the degree of relational coordination within the general practice
	GPs rating of the degree of relational coordination with the endocrinology department
	GPs rating of using virtual conferences based on the Technology Acceptance Model
	The extent to which the practice staff is confident managing T2D in general
	The extent to which the practice staff is confident managing T2D and ischemic heart disease, stroke, peripheral artery disease, and heart failure
	The extent to which the practice staff is confident managing T2D and blood pressure
	The extent to which the practice staff is confident managing T2D and kidney disease
	The extent to which the practice staffs is confident managing T2D and cholesterol
	Practice staffs’ rating of the degree of relational coordination within the general practice
	Practice staffs’ rating of the degree of relational coordination with the endocrinology department
	Practice staffs’ rating of using virtual conferences based on the Technology Acceptance Model

The secondary patient outcomes concern the percentage of patients with T2D alongside, respectively: HbA1c < 58 mmol/L, HbA1c < 53 mmol/L, blood pressure < 140 mmHg, blood pressure < 130 mmHg, low-density lipoprotein (LDL) > 2.5 mmol/L, microalbuminuria, and LDL > 1.8 mmol/L.

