### Statistical analysis plan

Statistical significance is expressed in 95% two-sided confidence intervals. A *p*-value of < 0.05 will indicate statistical significance.

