#### Difference between intervention and control group

The main analysis concerns the difference between the intervention and control group at month 12. Data from the Diabetes Overview and general practice survey are analysed using simple, multiple, and logistic regression analyses. Analysis is done according to the intention-to-treat principle to test if the groups differ in terms of outcome measures. The analysis of survey data will take into account cluster effects using the intra-cluster correlation coefficient. Using *t*-test and *Χ*^2^ tests, depending on the outcome measure, it will be determined if randomization has resulted in systematically different groups. Survey data are tested to determine if questions or indices of questions are internally consistent (Cronbach alpha). In the regression analyses, control variables at the individual (e.g., seniority) and practice level (e.g., form and size of practice) are tested to determine its influence on survey outcomes.

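### Six GP competence outcomes are named primary, but the multiplicity correction covers only the three clinical primaries, which leaves the six under the general 0.05 level

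*Protocol article*

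**What the plan says.** Under Outcomes, Clinical outcomes, the protocol article opens its multiplicity rule with "To account for multiplicity, we use the Bonferroni correction method to adjust the" and limits the adjustment to the p-"values of the three primary clinical outcomes". A null hypothesis in that set is rejected only if the p-"value is less than 0.0167 (i.e., 0.05/3").

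Table 2, in the same section, has a separate block of primary competence and organization measures. It holds six GP items. The first is "The extent to which the GP is confident managing T2D in general"; the others cover skill in decisions, and confidence with cardiovascular disease and heart failure, blood pressure, kidney disease and cholesterol. Study aim and objectives also calls these a primary objective, in five bullets because general confidence and skill share one.

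The Statistical analysis plan section sets the general rule: "Statistical significance is expressed in 95% two-sided confidence intervals", and a p-"value of < 0.05 will indicate statistical significance". The subsection on the difference between the groups analyses the survey by regression. It gives no adjusted level, order of testing or composite for the competence items.

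**The concern.** The article accepts that three primary outcomes tested together need a correction and supplies one. It then names six more outcomes primary and supplies none, without giving a reason for the difference. Read as written, one primary set has its error held at 5% and the other does not.

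Competence is one of the two parts of the stated aim, and the Dissemination plan foresees a separate article on general practice outcomes. The competence result is therefore likely to be read on its own. If one favourable item out of six were enough to report improved competence, that claim would carry a false-positive risk well above the level the plan accepts for its clinical claim.

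**Working it through.** **Inputs from the protocol article**
- Clinical primaries: 3, each at 0.05/3 (Clinical outcomes).
- Competence primaries: 6 (Table 2).
- General level: 0.05, two-sided (Statistical analysis plan).

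**Input not in the article**
- Correlation between the six test statistics. It is assumed equal for all pairs and varied from 0 to 0.95.

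**Step 1: the plan's own figure.** 0.05/3 = 0.01667, which rounds to the stated 0.0167. The chance of at least one false finding among the three is 1 − (1 − 0.05/3)³ = 4.9% if independent. It is at most 3 × 0.05/3 = 5% under any dependence.

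**Step 2: the competence set at 0.05, independent tests.** 1 − 0.95⁶ = 26.5%.

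**Step 3: the same with correlated items.** Six z-statistics were simulated as √ρ·C + √(1 − ρ)·Eᵢ, where C and the Eᵢ are independent standard normal, with 1,000,000 draws for each ρ. The second column counts draws in which any |z| exceeds 1.96. The third counts only results that favour the intervention, for which a single test has a nominal 2.5%.

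| Assumed ρ | Any false finding | In favour of the intervention |
|---|---|---|
| 0 | 26.5% | 14.1% |
| 0.3 | 24.1% | 12.2% |
| 0.5 | 20.8% | 10.4% |
| 0.7 | 16.4% | 8.2% |
| 0.9 | 10.8% | 5.4% |
| 0.95 | 8.9% | 4.4% |

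The first column of results reaches 5% only at ρ = 1, when the six items carry identical information.

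**Step 4: sensitivity to the count.** With five outcomes, as the objectives are bulleted, the risk is 1 − 0.95⁵ = 22.6% if independent and 18.3% at ρ = 0.5.

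**Step 5: after extending the plan's own rule.** The cut-off becomes 0.05/6 = 0.0083. The chance of at least one false finding is then 1 − (1 − 0.05/6)⁶ = 4.9% if independent, 4.1% at ρ = 0.5, and at most 5% under any dependence.

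**The case against.** **The rule for the six is inferred.** The article condenses a longer plan. The correction sentence sits under a clinical heading and does not mention competence. The general 0.05 sentence does not mention even the 0.0167 cut-off, so it is hardly a worked-out decision rule. This stands so far: nowhere does the text say outright that each competence item is tested at 0.05. It does state the scope of the correction and the default level, however, and 0.05 is what remains for the six when the text is followed. That is more than a detail left to a later document.

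**No passage says that one significant item establishes improved competence.** The objectives list separate questions, and reading each on its own can be argued for. This stands as a condition: the error over the whole set matters if any single success is taken to support the competence aim. Nothing in the article rules that reading out.

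**The items will be correlated.** They are ratings by the same GP in one survey, so independence is implausible and 26.5% is not a best estimate. This also stands, and it is why the range is shown.

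**The section on competence outcomes speaks of the primary outcome in the singular.** It defines no composite, and Table 2 lists six measures.

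Three stronger readings may tempt a reader, and the article does not support them.
- *Cronbach alpha will pick the primary variable after the data are seen.* The text says only "Survey data are tested to determine if questions or indices of questions are internally consistent (Cronbach alpha"). It does not make alpha decide between items and an index, and the check could equally concern the survey's technology-acceptance and relational-coordination measures.
- *Unblinded self-report makes a chance positive easier to obtain.* Lack of blinding can bias the ratings. It does not raise the chance error of a test when there is no effect, and a multiplicity correction would not remove such bias.
- *All nine primaries should be judged as one family.* The plan separates clinical from competence objectives, and control within each is a defensible choice. The point here is the error within the competence set.

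**Conclusion.** The point holds in conditional form. The plan corrects one primary family and leaves the other under the general 0.05 level. If any one significant competence item is read as support for the competence aim, the risk of a false finding runs from 26.5% (independence) down to about 11% (correlation 0.9), against at most 5% for the clinical family.

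The figures rest on six two-sided tests, no true effect on any item, and an assumed common correlation. The three clinical primaries and their 0.0167 cut-off are unaffected. This should be put right before the month-12 analysis, but it does not threaten the main clinical conclusion.

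**What to change.** **Preferred.** Add to the outcomes section that the six GP competence items form a second primary family, tested by Holm at a family level of 0.05. The smallest p-value is then compared with 0.05/6 = 0.0083; plain Bonferroni would use that cut-off for all six. Amend the Statistical analysis plan section to say that the general 0.05 level does not apply to individual outcomes in either primary family.

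**Alternative.** Before month-12 data are analysed, name one composite of the Table 2 GP items as the single primary competence outcome, tested once at 0.05, with the items as supportive results. State how it is built. The data collection section lists cardiovascular disease and heart failure as separate survey themes (seven in all), while Table 2 merges them into one item, so the composite cannot be computed from Table 2 as it stands.

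**Cost.** Either change is about a paragraph of text. The first sets a stricter threshold: an item with an assumed 80% power at 0.05 has z = 1.96 + 0.84 = 2.80, and against the critical value 2.64 for 0.0083 its power is Φ(2.80 − 2.64), about 57%. The second gives one overall claim in place of six and gains power only if effects are similar across items. Under the same assumption and ρ = 0.5, the mean of six has standard deviation √((1 + 5 × 0.5)/6) = 0.764.
- Equal effects on all six: z = 2.80/0.764 = 3.67, power about 96%.
- Only one item moves: z = (2.80/6)/0.764 = 0.61, power about 9%.

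The article gives no power figure for the competence outcomes, so the sponsor should choose by which pattern of effect it expects.

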#### Competence and organization outcomes

Table 2 shows the primary and secondary outcome measures at the general practice level. The primary outcome concerns the competence of the GPs with regards to managing T2D and their patient population living with T2D. The secondary outcome measures are (a) the competence of the practice staff with regards to co-managing patients with T2D and (b) GPs and practice staffs’ rating of the degree of relational coordination within the general practice, their rating of the degree of relational coordination with the endocrinology department, and their rating of using virtual conferences.

### Recruitment strategy for achieving adequate enrolment

The recruitment strategy relies on six elements. First, GPs are reimbursed for participating in the conferences, collecting data and answering the survey. Second, formal collaboration with the chairman of the Local Association of General Practitioners in Aarhus municipality (PLO-Aarhus) and a representative of the Regional Association of General Practitioners from the Central Denmark Region (PLO-M). Third, regional-level support through a project grant from the Regional Committee for Quality and Development in General Practice to reimburse GPs for their participation in the study. Fourth, two types of official PLO newsletters (one from PLO-Aarhus and another from PLO-M) containing information about the project and how to participate is distributed to GPs in Aarhus Municipality. Fifth, GPs will receive project information through ground mail and electronic mail (via the Danish public electronic mailbox system, e-boks Business) using publicly available data from the Central Business Registration. Sixth, GPs will learn about the project by calling them on telephone. The GPs will be contacted in a random order by generating a computerized random sequence of ID numbers from 1 to 100.

